### Objectives

1.1

The THRIVE-CP trial evaluates the effectiveness of incorporating Music Motion Feedback into home-based motor training for adolescents and young adults with CP compared to home-based motor training without Music Motion Feedback. We hypothesize that the Music Motion Feedback group will demonstrate greater improvements in real-world movement behavior, functional improvement, limb function, and perceived goal performance than the control group. Additionally, we expect the Music Motion Feedback group to attend and adhere more to the training program.

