### Criteria for modifying or discontinuing interventions and participation

2.9

Changes to the motor training program may occur outside of the standard progression or regression, provided the goals are maintained. These occur during scheduled virtual conferences, either at the participants' request, in response to reported musculoskeletal issues, or due to safety concerns. If a participant requires surgery affecting functional ability and training during the trial, faces an illness that necessitates more than a week of hospitalization, or if Botox-naïve participants receive injections, their participation will be discontinued. If a participant withdraws from the trial, discontinues the motor training program, or is lost to follow-up, they will be asked whether the collected data can be used for analysis.

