#### Sample size

2.13.2

The sample size calculation is based on a systematic review and meta-analysis of controlled trials assessing extrinsic feedback on recovery and motor learning in individuals with brain injuries. The analysis found a significant Standardized Mean Difference of 0.76 with participants in identical motor training programs, differing only in feedback provision [16]. With 58 participants, we will attain a statistical power of 81.8 %. To account for potential dropouts, we plan to enroll 70 participants (35 in each group).

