#### Statistical methods

2.13.3

The distributions of continuous data will be assessed using Quantile-Quantile (Q-Q) plots, histograms, and the Shapiro-Wilk test. Normally distributed continuous data will be analyzed with parametric statistics. If normality is not met, a logarithmic transformation will be applied. Ordinal data will use non-parametric statistics. Categorical data will be presented as frequencies and percentages. An intention-to-treat analysis will include data from all trial participants.

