##### The primary outcome

2.13.3.1

A linear mixed-effects model (LMM) will analyze the percentage change in real-world targeted extremity movement from baseline (T1) to 12 weeks (T2) and 24 weeks (T3). The model will include fixed effects for Group (Music Motion Feedback vs. Control), Time (T1-T2, T1-T3), and their interaction (Group × Time), adjusted for baseline extremity movement time and sex. A random intercept for each participant will account for individual differences in baseline differences, and a random slope for Time will model variability in improvement rates. If residuals indicate non-normality, a logarithmic transformation will be performed.

Given the moderate sample size, the analysis will be conducted using restricted maximum likelihood estimation. A Holm-Bonferroni correction will be applied to adjust for multiple comparisons. A planned subgroup analysis will evaluate age group effects (adolescents vs. young adults).

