#### Missing data

2.13.4

To address dropouts and discontinuations, including participants who meet exclusion criteria during the trial, we will use multiple imputations to generate overall estimates and standard errors that account for the uncertainty associated with the imputation.

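### Stopping training or being lost to follow-up triggers, as withdrawal does, a refusable request to use data already collected; any refusal would defeat the all-participants analysis

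*Protocol article*

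**What the plan says.** Section 2.9 (Criteria for modifying or discontinuing interventions and participation) covers three events in one sentence. The first is trial withdrawal; the sentence then names the other two and gives the rule for all of them: "discontinues the motor training program, or is lost to follow-up, they will be asked whether the collected data can be used for analysis". The three events get the same treatment, and the question is put after the event has happened.

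Section 2.13.3 (Statistical methods) sets the analysis population: "An intention-to-treat analysis will include data from all trial participants". Section 2.13.4 (Missing data) adds: "To address dropouts and discontinuations, including participants who meet exclusion criteria during the trial, we will use multiple imputations". The primary model in section 2.13.3.1 analyses percentage change from baseline and is "adjusted for baseline extremity movement time and sex".

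On how the arms may differ, the Objectives state: "we expect the Music Motion Feedback group to attend and adhere more to the training program".

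The article does not say what happens to a randomised participant who answers no or does not answer. Nor does it say whether someone who only stops training is still assessed at 12 weeks (T2) and 24 weeks (T3).

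**The concern.** Intention-to-treat analysis exists largely to keep people who stop the assigned programme. Section 2.9 invites exactly those people to take their data out, while completers are never asked. Whether a randomised participant is analysed then depends on a choice made after randomisation, possibly in light of how training went.

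Three things would be at stake if anyone refused:

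- **Primary outcome.** Any T2 measurement from someone who stopped training but was still assessed is lost, as is the baseline value needed for the percentage change and the adjustment.
- **Adherence.** Section 2.13.3.2 compares low, medium and high categories of attendance and practice time. Early stoppers probably belong in the low category, so refusals would thin that category.
- **Harms.** Section 2.11 compares adverse events, including pain and fatigue, by relative risk. An event that caused someone to stop could be removed with the rest of their data.

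**Working it through.** **1. The passages side by side.** Section 2.9 allows a refusal. Section 2.13.3 allows no exclusion. Both hold as long as nobody refuses; with one refusal they cannot both hold. Section 2.13.4 does not close the gap. Imputation needs something observed on the person, and a refusal covers the baseline and app data as well. What remains could be little more than the allocated arm. Missing at random would also be doubtful if refusal depended on progress.

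**2. The planned size.** Inputs from section 2.13.2: "The analysis found a significant Standardized Mean Difference of 0.76"; "With 58 participants, we will attain a statistical power of 81.8" %; "we plan to enroll 70 participants (35 in each group"). The article gives no alpha for this calculation; two-sided 0.05 is assumed.

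- Two-sample comparison, difference 0.76 SD, 29 per arm: power 81.2% (noncentral t) or 82.5% (normal approximation). The stated 81.8% is reproduced to within a point.
- Dropout allowance: 70 − 58 = 12, and 12/70 = 17.1%. Check: 58/(1 − 12/70) = 70.
- Power by number analysed (t): 70 gives 88.0%, 64 gives 84.9%, 58 gives 81.2%, 56 gives 79.8%, 52 gives 76.7%.

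The allowance protects precision down to 58 participants. It does nothing about selection.

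**3. Illustrations of selective refusal.** The documents give no stopping rate, refusal rate or outcome gap, so every input here is assumed.

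*Both arms, all stoppers refuse.* Suppose 12 stop, split 9 and 3, and stoppers change 0.5 SD less than completers. Deleting k stoppers from an arm of 35 raises that arm's mean by 0.5 × k/35. The difference between arms shifts by 0.5 × (9 − 3)/35 = 0.086 SD, and 0.086/0.76 = 11%.

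*Same, 25% refuse.* Simple scaling gives 0.25 × 0.086 = 0.021 SD, about 3% of 0.76. Keeping the other stoppers in the means gives slightly less:

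- Arm with 9 stoppers: 0.5 × (9/35 − 6.75/32.75) = 0.0255.
- Arm with 3 stoppers: 0.5 × (3/35 − 2.25/34.25) = 0.0100.
- Net shift: 0.0155 SD, about 2% of 0.76.

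*One arm only.* If k of 35 refuse and their mean is m SD below their arm's mean, the arm mean rises by k × m/(35 − k):

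| k | m = 0.5 | m = 1.0 |
|---|---|---|
| 2 | 0.03 SD | 0.06 SD |
| 4 | 0.06 SD | 0.13 SD |
| 6 | 0.10 SD | 0.21 SD |

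The last row is 14% to 27% of 0.76.

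*Even split.* With equal numbers and the same gap in both arms, the shift cancels.

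*Direction.* If stoppers do worse and are more common among controls, deleting them shrinks the apparent benefit. If they are more common in the feedback arm, it inflates it.

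**The case against.** The strongest reply is that the plan means to keep these people. Section 2.13.4 imputes for dropouts and discontinuations, and section 2.9 never says that data are deleted by default; asking may be an attempt to retain them. That is fair as to intent. A reader might infer that the plan contradicts itself outright, and the documents do not support that: the conflict arises only on a refusal. But the request is a stated rule, and a statistical analysis plan cannot restore data that a participant has refused.

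A reader might also take 11% as the expected bias. It is not. It assumes that everyone refuses and a 9 to 3 split. It also compares deletion with full outcome data on all 70, whereas the 12 are the dropout allowance, and many of them would have no T2 value whatever section 2.9 said. For those people the rule adds only the loss of baseline and app data. Its separate effect on the primary outcome falls on people who stop training, are assessed at T2 and then refuse, and the documents give no way to count them.

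Two further limits stand. It is tempting to say that nobody lost to follow-up can be asked, but the article does not define the term, and some may be reachable directly or through a caregiver. And the consent text is not shown, so what participants agreed about data retention is unknown.

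**Conclusion.** The concern holds in a conditional form. Section 2.9 gives stopping training and loss to follow-up the same refusable data request as withdrawal from the trial. Any refusal makes the all-participants analysis unattainable and removes what imputation would need for that person. Selective refusal is plausible, since the trial itself expects adherence to differ by arm, but this is an inference; the documents report nothing on refusals.

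The size cannot be stated from the documents. It may be zero. The illustrations, about 2 to 3% of the planned effect at 25% refusal and 11% at full refusal, rest on the assumed 9 to 3 split and 0.5 SD gap. Neither is an estimate or a bound, as the one-arm table shows. The change is worth making because it is cheap and because data refused under the present rule cannot be recovered.

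**What to change.** Rewrite the sentence in section 2.9 so that the three events are handled separately:

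- **Stopping the training programme:** ask no new permission, keep all collected data in the analysis under the original consent, and still invite the participant to T2 and T3.
- **Loss to follow-up:** ask no new permission, and use everything collected up to the last contact under the original consent.
- **Explicit withdrawal of consent:** the only event that may carry a data-removal option, on terms set by the consent form and applicable data-protection law.

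Report the number of removals by arm.

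The cost is a wording change to the protocol and, if the consent form does not already cover retention, one there too, with an ethics notification. The assessments for those who stop training are ones already scheduled for every participant. The change should be made early, before any data are refused.

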### Outcomes

2.10

Baseline (T1) and outcome assessments (T2, T3) will be performed on weekdays within a week before intervention commencement (T1), within a week after the end of intervention (T2), and 24 weeks after intervention initiation (T3). Assessments will be conducted at approximately the same time of day for each participant to minimize intraday variability. The primary endpoint is T2. Please view the assessment timeline in Fig. 2.

**Fig. 2 fig2:**
[figure not shown]
SPIRIT figure. Schedule of enrollment, interventions, and assessments. **Note:***t*_1_ baseline, *t*_2_ 12 weeks (primary endpoint), *t*_3_ 24 weeks, *t*_4_ 26 weeks. Gross Motor Functional Classification Scale-Expanded and Revised (GMFCS-E&R), Action Research Arm Test (ARAT), Gross Motor Function Measure-66 (GMFM-66), 6-min walk test (6MWT), Canadian Occupational Performance Measure (COPM). (a) Systematic inquiry of potential events during virtual conferences. (b) Data will be collected continuously through the TIA app. (c) Only the Music Motion feedback group can be tracked for staying at or above the intensity threshold. (d) Involves completing the participant's involvement in the trial, including final data review, administrative tasks, and confirming that all study procedures have been appropriately completed.

#### Primary outcome

2.10.1

The primary outcome is the percentage change in real-world daytime movement of the targeted extremity (right or left arm or leg). We hypothesize this reflects the impact of the anticipated increase in capacity from motor training programs on real-world movement behaviors. Data will be collected from seven IMUs worn by participants for 72 consecutive hours and analyzed using a deep-learning neural network. The methodology details have been previously described [20]. IMUs will be attached with adhesive patches on the sternum, wrists, thighs, and lower legs to collect 3-axis accelerometer and gyroscope data. A custom neural network converts the signals into images and processes them through several convolutional layers, extracting features to recognize movement behaviors. Movement behaviors beyond limb movement will be utilized for exploratory outcomes. Daytime will be recorded in participant logs, noting the times in bed, lights out, devices off, wakefulness, and when they leave bed.

#### Secondary outcomes

2.10.2

The secondary outcomes will evaluate changes in capacity and function. Participants will be split based on goal-directed training for upper or lower extremities. The effects of upper-extremity training will be assessed using the Action Research Arm Test (ARAT) total score, isometric arm strength, and maximum grip strength. For lower-extremity assessment, the Gross Motor Function Measure-66 (GMFM-66), isometric leg strength, and the 6-min walk test will be applied. In addition, attendance and adherence will be monitored as process measures.

**ARAT** consists of 19 items across four dimensions: grasp, grip, pinch, and gross arm movement. Each item is rated on a 4-point ordinal scale ranging from normal performance to inability to perform any part of the test. The maximum total score is 57 points, with higher scores indicating greater functioning [21].

A hand dynamometer will determine the percentage change in **maximum hand grip strength** (Jamar Technologies, Horsham, PA, USA). Participants will squeeze the device maximally. After one practice trial, three measurements will be taken, with rest periods. The highest value will be recorded as the maximum grip strength.

**GMFM-66** is a 66-item observational assessment divided into five dimensions: Lying and rolling, sitting, crawling and kneeling, standing, walking, running, and jumping. Each performance is rated on a 4-point ordinal scale: Does not initiate task, Initiates task (<10 %), Partially completes task (10–99 %), and Completes task (100 %). Calculations of GMFM-66 scores require the use of a computer program, Gross Motor Ability Estimator-3 (GMAE-3) [22].

**6MWT** measures submaximal aerobic and functional gait capacity. Able participants will walk 6 min on a 30-m walkway with the enclosed corridor length marked at every 3-m interval. Cones mark turnaround points. The total distance walked over the 6 min is used as the score [23].

**Isometric strength** will be assessed using handheld dynamometry by measuring maximal isometric force for muscle groups. Three measurements will be recorded with rest periods, and the highest value (kilogram force) per muscle group will be recorded as the maximum.

The TIA app will collect **attendance and adherence data**, which includes daily logins, session duration, and the time spent moving the targeted extremity.

For participants in the Music Motion Feedback group, daily intensity thresholds and time spent within these thresholds will also be recorded and descriptively reported.

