### Eligibility criteria

2.3

Individuals with CP aged 15 to 25 at enrollment are eligible to participate if they have sensorimotor deficits in at least one limb and are classified within GMFCS-E&R levels I-V. They must show motivation to develop new motor skills or recover lost ones, as indicated by their or their proxy's ability to express a specific goal they wish to achieve. They must be able to follow instructions independently or with caregiver support and be capable of providing informed consent to participate. Individuals will be excluded from participation if they have dyskinetic CP, significant health risks, have undergone major orthopedic or neurosurgical procedures within six months preceding enrollment or planned during the intervention period, or minor procedures that could temporarily affect training or movement behavior within one month before enrollment or during the trial. Eligibility for borderline cases is determined by the principal investigator in consultation with the treating physician. Botulinum neurotoxin type A (BoNT-A)-naïve individuals will be excluded if they have received intramuscular injections within three months before baseline. Individuals undergoing routine BoNT-A injections are eligible, and injections in muscles not directly targeted by the training program do not preclude participation.

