##### Secondary outcomes

2.13.3.2

Attendance (number of training sessions) and adherence (active practice time) will each be categorized based on the prescribed dose achieved: low (<33 %), medium (33–66 %), and high (>66 %). Chi-square tests will compare the two groups' attendance distribution and adherence levels.

The analysis of other secondary outcomes will follow the same approach as the primary outcome, using LMM.

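### Grip strength is fixed as percentage change, which is undefined at zero baseline grip and unstable near it; analyse it in kg and state own-baseline adjustment for the secondary outcomes

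*Protocol article*

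**What the plan says.** Section 2.10.2 (Secondary outcomes) introduces grip with "A hand dynamometer will determine the percentage change in" maximum grip strength. After a practice trial and three measurements, "The highest value will be recorded as the maximum grip strength". The other strength measure in that section is recorded in kilogram force, the walk test as a distance, and ARAT and GMFM-66 as scores. Only grip is called a percentage change.

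Grip belongs to the upper-limb set: "Participants will be split based on goal-directed training for upper or lower extremities". Section 2.3 admits people with "sensorimotor deficits in at least one limb and are classified within GMFCS-E&R levels I-V" and sets no floor for hand function. Section 2.13.1 explains the choice of percentage over absolute change, but only for real-world extremity movement, because that varies widely between participants.

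On analysis, section 2.13.3.2 says: "The analysis of other secondary outcomes will follow the same approach as the primary outcome, using LMM". The primary model in section 2.13.3.1 is "adjusted for baseline extremity movement time and sex", and its fallback reads: "If residuals indicate non-normality, a logarithmic transformation will be performed". Section 2.13.3 promises an intention-to-treat analysis with data from all participants. Section 2.13.4 applies multiple imputation to dropouts and discontinuations.

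**The concern.** A percentage change divides by the baseline value. In the upper-limb group, some participants may have a baseline grip of zero or close to it. At zero the outcome has no value. Close to zero, an ordinary gain or an ordinary measurement error becomes a very large percentage, and a few weak hands can determine the group mean. The stated safeguards (log transformation, imputation of dropouts) were not written for this case.

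The stakes are limited to one secondary outcome, but that outcome is analysed only in the arm subset, where each lost or extreme value weighs more. A correction made only to the primary outcome would leave the grip definition in section 2.10.2 in place.

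A smaller question is attached. The secondary models borrow the primary model's approach, and the only baseline covariate named there is movement time. The article does not say in words that each secondary outcome is to be adjusted for its own baseline.

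**Working it through.** **1. The plan's own figure.** None is given for grip. The only power figure is for the primary comparison: 81.8% with 58 participants at a standardized mean difference of 0.76. With 29 per arm and two-sided 5% (assumed), 0.76 × √(29/2) = 2.894 and Φ(2.894 − 1.960) = 82.5%; the noncentral t version gives 81.2%. The figure reproduces, and this point does not touch it.

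**2. The ratio.** Percentage change = 100 × (follow-up − baseline) / baseline. For the same assumed gain of 2 kg:

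| Baseline (kg) | 30 | 20 | 10 | 5 | 2 | 1 | 0.5 | 0 |
|---|---|---|---|---|---|---|---|---|
| Change (%) | 6.7 | 10 | 20 | 40 | 100 | 200 | 400 | undefined |

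One participant at 1 kg carries the weight of twenty participants at 20 kg (200 / 10 = 20).

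**3. The log fallback.** A percentage change is zero when grip is unchanged and negative when it falls. The logarithm exists in neither case, so the transformation cannot be applied to this outcome as defined.

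**4. The analysis set.** A zero-baseline participant can be fully observed at all visits and still have no defined outcome. Such a person is neither a dropout nor a discontinuation, so the imputation in section 2.13.4 does not cover the case.

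**5. Power.** The article gives no grip distribution and no size for the upper-limb subset, so every input here is an assumption: 15 per arm (about half of 58 in total) and a baseline–follow-up correlation of 0.9. A t-test on percentage change, with zero baselines dropped, is compared with ANCOVA on kg. The normal shape has values below zero set to zero. The lognormal shape has the same means and SDs, with the correlation on the log scale. Figures are good to a few points.

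| Baseline mean (SD), true gain | Normal cut at 0: % change vs kg | Lognormal: % change vs kg |
|---|---|---|
| 20 (8), +4 kg | 57% vs 83% | 89% vs 85% |
| 14 (9), +4 kg | 32% vs 75% | 87% vs 75% |
| 20 (8), +30% | 71% vs 96% | 98% vs 96% |
| 14 (9), +30% | 27% vs 69% | 73% vs 64% |

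Under the first shape, percentage change loses 25 to 43 points; under the second it gains 2 to 12.

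The shape also decides whether zeros occur at all. For the normal, P(below 0) is Φ(−20/8) = 0.0062 and Φ(−14/9) = 0.060. At least one zero among 30 then has probability 1 − 0.9938^30 ≈ 17% and 1 − 0.940^30 ≈ 84%. Under the lognormal, zeros are impossible by construction.

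A further simulation (29 per arm, right-skewed grip with median 15 kg, 2 kg gain, measurement error constant in kg) gave percentage change 60%, 46%, 40% and 33% power when 0, 5, 10 and 20% of participants had very low grip. ANCOVA on kg stayed at about 84%. The mean number of zero baselines per trial was 0.03, 0.9, 1.7 and 3.3. So the result depends on whether variation is constant or proportional as well as on the shape of the distribution.

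**6. The covariate wording.** In section 2.13.3.1, baseline movement time is the primary outcome's own baseline. If a secondary change score were really left unadjusted for its own baseline, and movement time explained none of it, the required sample relative to ANCOVA would be 2(1 − ρ)/(1 − ρ²) = 2/(1 + ρ). That is 1.33, 1.25, 1.18, 1.11 and 1.05 for assumed ρ of 0.5, 0.6, 0.7, 0.8 and 0.9.

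**The case against.** **Covariate.** A reader might infer that ARAT, GMFM-66, walking and strength would be adjusted for IMU movement time and not for their own baselines. The text does not say this. Section 2.13.3.2 lists no covariates. Since the primary model's covariate is that outcome's own baseline, following the same approach more naturally means each outcome's own baseline. This objection stands, and only a one-sentence clarification remains.

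**Power.** A reader might also infer that percentage change costs grip a large share of its power. That rests on a distribution cut at zero. With the same means and SDs in a lognormal shape, percentage change does as well or better. This stands too: neither the size nor the direction of the effect is established.

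**Frequency.** GMFCS-E&R grades gross motor function and not the hand, the discussion projects 70% of participants at levels I–II, and participants must be able to follow instructions and work towards a motor goal. Zero grip may be rare. This is fair, and the frequency must be left open. Equally, nothing in the eligibility criteria excludes it.

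**Left to the analysis plan.** A rule for zero readings and a covariate list per model are ordinary analysis-plan content, and their absence from an article is no fault. That is correct, but the grip definition is not an omission. The article states it, and a later plan that follows it inherits the undefined ratio.

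**Conclusion.** The point holds for the grip definition. As stated, the outcome is undefined at zero baseline, unstable close to it, and not rescued by the log transformation or by imputation of dropouts. Any zero-baseline participant would be lost from the intention-to-treat set for grip. These conclusions follow from the definition and need no assumption about the data. How many participants are affected, and what happens to power, cannot be determined from the document; the simulated figures show only how strongly the answer depends on the assumed grip distribution and error.

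The covariate wording is an ambiguity to clear up, not an error. The 5 to 33% larger sample would apply only if own baselines were truly left out, with correlations between 0.9 and 0.5. Overall this is a limited point about one secondary outcome in one subset, worth making because the correction is nearly free.

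**What to change.** - **Section 2.10.2:** define grip as maximum grip strength in kg, in line with the kilogram-force recording of isometric strength. Analyse it at T2 and T3 with baseline grip as covariate, and report percentage change descriptively, giving the number of participants for whom it is undefined.
- **Section 2.13.3.2:** add one sentence stating that each secondary outcome analysed by LMM is adjusted for its own baseline value, and not for IMU movement time.
- **Log fallback:** kg values are defined at zero but their logarithm is not, so do not make the log transformation the automatic fallback for grip.

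The cost is wording in the protocol and the statistical analysis plan, which section 2.13 schedules before the last participant's first visit. No new data are needed. The possible price is some power if grip is strongly right-skewed with no near-zero values and proportional variation: 2 to 12 points in the lognormal scenarios above.
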